### Interim analyses {21b}

Do not apply. Interim analysis is not contemplated through discussion with the founder and partners

### Methods for additional analyses (e.g., subgroup analyses) {20b}

We also plan a subgroup analysis comparing the multimodal and the unimodal group, with the control group. In these cases, using a repeated-measures ANOVA between the two groups mixed with covariates such as age, sex, and baseline pain is planned for each multimodal and unimodal group.

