**Methods:**

The aim of this study is to implement an individualized therapy and aftercare program within the rehabilitation offer of the German Pension Insurance in the area of orthopedics and to examine its success and sustainability in comparison to the previous standard aftercare program.

The study is a multicenter randomized controlled trial including 1204 patients from six orthopedic rehabilitation clinics. A 2:1 allocation ratio to intervention (individualized and home-based rehabilitation aftercare) versus the control group (regular outpatient rehabilitation aftercare) is set. Upon admission to the rehabilitation clinic, participants in the intervention group will be screened according to their psychosocial risk profile. They could then receive either unimodal or multimodal, together with an individualized training program. The program is instructed in the clinic (approximately 3 weeks) and will continue independently at home afterwards for 3 months. The success of the program is examined by means of a total of four surveys. The co-primary outcomes are the Characteristic Pain Intensity and Disability Score assessed by the German version of the Chronic Pain Grade questionnaire (CPG).

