### Trial design {8}

Multicenter intervention trial: A randomized controlled prospective longitudinal intervention study (RCT) will be conducted at several hospitals in the regions of Berlin-Brandenburg and Central Germany. The study includes a total of four measurement points: at rehabilitation clinic admission (t0: baseline), at the end of the rehabilitation stay (t1), at the end of the 9-week home training phase (t2), and 3 months after the end of the accompanied training (t3: follow-up). Questionnaires and functional and clinical data are collected. After signing the informed consent, patients will be randomly allocated to the intervention group (including 2 subgroups arms; unimodal and multimodal intervention) or the control group (treatment as usual) using a 2:1 ratio. The subgroup allocation within the intervention group, either to a unimodal or a multimodal therapy will follow the Risk Stratification Index (RSI) [11]. An additional assignation to modules within the multimodal group will follow the Risk Prevention Index (RPI-S) [11] (see Figs. 1, 2, and 3.). The initial random 2:1 ratio allocation should ensure enough patients in each subgroup arm (unimodal or multimodal) to be able to analyze the differences between both and confirm the discrimination’s ability of the screening tool in this population (see Fig. 4). The framework of the trial is superiority.

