## Interventions

### Explanation for the choice of comparators {6b}

The intervention group will receive a home-based exercise program after an initial center-based training. Currently, in Germany, there is no offer of a home-based program, which would allow patients a soft transition from the rehabilitation clinic to their everyday life. Likewise, rural areas have difficulty accessing the programs implemented exclusively in rehabilitation centers and clinics [13, 15].

In line with recent studies, diverse therapy modules tailored to individual patient needs, when based on an early screening for psychosocial risk factors, enable an optimal therapy for chronic back pain [10, 16, 17]. Accordingly, an initial differentiation between low-risk (unimodal) and high-risk (multimodal) groups through the RSI score, followed by an additional module individualization by the RPI-S score, is encouraged [11].

The intervention incorporates behavioral therapy modules together with exercise in the multimodal group. A combined approach of sensorimotor training, deflection, and body scan targets neurobiological adaptation processes. Furthermore, psychoeducation involving caregivers increases compliance and dismantles unfavorable support structures in the social environment [17].

The control group will receive the current rehabilitation aftercare offered by the German pension insurance “DRV” in the rehabilitation centers. It is relevant and appropriate to compare the new program with the “treatment as usual” program already implemented.

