### Outcomes {12}

#### Risk stratification

##### Risk Stratification Index (RSI) and Risk Prevention Index (RPI-S)

The Risk Stratification Index (RSI) is a screening tool that allows an estimation of the risk of low back pain chronicity (1-year prognosis) through psychosocial risk factors. It includes baseline pain, unhappiness, social support and status, distress (chronic worries), work dissatisfaction, misfortune, pain persistence, sleep problems, and other health care issues such as medication history and insurance status [11].

The Risk Prevention Index (RPI-S) is a screening tool that identifies further individual therapy needs of low back patients, based on the risk within four psychosocial domains (distress, pain experience, social environment, and medical care environment). It also incorporates expectations to exercise treatments [11].

Both screening tools were derived through LASSO (least absolute shrinkage and selection operator) models, which covered yellow, black, and blue flag factors for chronic back pain and disability, as well as demographic and protective factors [32].

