## Discussion

The main purpose of the study is to compare the efficacy of an individualized home-based aftercare program to the regular outpatient care for the rehabilitation of back pain. For this purpose, a randomized controlled trial is performed. We expect to have improvements in terms of pain, work ability, patient compliance, and acceptance in our intervention compared to the standard program.

The study helps to ensure that particularly patients living far away from clinical rehabilitation centers receive individualized care.

Because the intervention consists of individualized programs (unimodal, multimodal, and their corresponding intervention modules) for different patient risks, we also expect to have a better response in other outcome measures such as health-related quality of life, subjective well-being, and sensation of pain. We will also explore whether changes in the outcomes occur within the intervention group (unimodal vs multimodal) and how these differences unfold over the follow-up measures. Regarding the comparison between these subgroups, the power of our study is here limited, since our sample size is only intended to compare the two randomized groups (main objective). Nonetheless, this study contributes to the research regarding integrative programs. The exercises and tasks of the program involved in the study are of value, since up to now, only limited data provide information on training individualization. Furthermore, implementation of psychosocial risk factors in low back pain research is limited [57].

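### Risk-selected unimodal and multimodal patients are each compared with a control group not divided by risk, so the subgroup contrasts are confounded by the RSI

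*Protocol article*

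**What the plan says.** Only intervention versus control is randomised, 2:1 and stratified by centre (protocol article, Trial design {8} and Sequence generation {16a}). Within the intervention group the programme is assigned by score. The section on comparators {6b} describes "an initial differentiation between low-risk (unimodal) and high-risk (multimodal) groups through the RSI score", and the abstract says that "participants in the intervention group will be screened according to their psychosocial risk profile". No equivalent step is described for controls.

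The Outcomes section {12} calls the RSI "a screening tool that allows an estimation of the risk of low back pain chronicity (1-year prognosis) through psychosocial risk factors". Besides baseline pain it lists, among others, unhappiness, social support, distress, work dissatisfaction, pain persistence and sleep problems.

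The section on additional analyses {20b} then states: "We also plan a subgroup analysis comparing the multimodal and the unimodal group, with the control group". The model is a repeated-measures ANOVA between two groups, and "covariates such as age, sex, and baseline pain is planned for each multimodal and unimodal group". Neither the RSI nor a risk stratum is named.

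Trial design {8} adds a further use of the subgroups. The 2:1 ratio "should ensure enough patients in each subgroup arm (unimodal or multimodal) to be able to analyze the differences between both", and that comparison is also meant to confirm that the screening tool discriminates in this population.

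**The concern.** Randomisation makes the whole intervention arm comparable with the whole control arm. It does not make the high-risk part of one arm comparable with all of the other, because the controls contain both high-risk and low-risk patients. If risk predicts outcome, the multimodal group starts with a worse prognosis than its comparator and the unimodal group with a better one. The planned covariates remove only the part of this imbalance that runs through age, sex and baseline pain.

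Risk-tailored care is the idea behind the programme, so readers will look to these contrasts to judge whether each branch works. A contrast that reflects who was selected could credit or discredit a branch wrongly.

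The comparison of unimodal with multimodal has a related problem. Every high-risk patient receives one programme and every low-risk patient the other, so the comparison cannot separate the tool's discrimination from a difference between the programmes.

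**Working it through.** The article gives no figure for this bias, so there is none to reproduce. The check derives the bias and puts a range on it.

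**Inputs from the article:** design effect d = 0.2 and correlation among repeated measures 0.57 (Sample size {14}; the latter from the pilot's disability score).

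**Assumed, because the article does not give them:** high-risk share p; gap δ, in SD, between high-risk and low-risk patients under the same care. Both co-primary scores run from 0 to 100 with higher meaning worse, so a positive bias makes a programme look worse.

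**Step 1: follow-up level, unadjusted.** The expected control mean is p × high + (1 − p) × low. Therefore:
- multimodal minus all controls = true effect + (1 − p)δ
- unimodal minus all controls = true effect − pδ

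The signs are opposite. Weighted by subgroup size the biases sum to zero: p(1 − p)δ − (1 − p)pδ = 0. This is why the overall intervention-versus-control comparison is untouched.

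**Step 2: follow-up level, adjusted for baseline pain.** Let δB be the gap at baseline and δF the gap at follow-up, and take 0.57 as the slope of follow-up on baseline. The biases become (1 − p)(δF − 0.57δB) and −p(δF − 0.57δB). With the same gap at both times this is (1 − p) × 0.43δ and −p × 0.43δ.

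| p | δ | Unadjusted: unimodal / multimodal | Adjusted: unimodal / multimodal |
|---|---|---|---|
| 0.5 | 0.3 | −0.15 / +0.15 | −0.06 / +0.06 |
| 0.5 | 0.5 | −0.25 / +0.25 | −0.11 / +0.11 |
| 0.5 | 0.8 | −0.40 / +0.40 | −0.17 / +0.17 |
| 0.3 | 0.3 | −0.09 / +0.21 | −0.04 / +0.09 |

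The adjusted columns are the relevant ones, because the plan adjusts for baseline pain.

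**Step 3: simulation.** With no treatment effect, 2:1 allocation, a median split on risk, a baseline-pain coefficient of 0.57 and a correlation between risk and pain of 0.3 to 0.7 (all but the allocation are assumptions), the adjusted bias was:
- 0.04 to 0.08 SD for a residual RSI coefficient of 0.1
- 0.09 to 0.15 SD for 0.2
- 0.14 to 0.23 SD for 0.3
- about zero only when the RSI added nothing to baseline pain

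With controls of the same risk stratum the bias was at most 0.01 SD in every scenario.

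**Step 4: dependence on the model term.** The primary analysis treats T0 as a repeated level. If the subgroup model does the same and the group-by-time term is tested without letting baseline pain act differently over time, the bias depends on δF − δB. With equal gaps it cancels. If the gap shrinks, for example from 0.5 to 0.3 (an assumption) with p = 0.5, the multimodal bias is 0.5 × (0.3 − 0.5) = −0.10, which favours multimodal.

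**Step 5: unimodal versus multimodal.** Multimodal minus unimodal = δ + (multimodal effect − unimodal effect). If δ = 0.3 and the multimodal programme lowers the score by 0.3 SD more than the unimodal one, the observed difference is 0 although the tool discriminates. The two terms cannot be separated within the intervention arm.

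**The case against.** The section does not say that the control group is left whole, and its covariate list is open-ended. A separate statistical evaluation plan is mentioned under Data management {19}, and the allocation flow charts are not visible here. Measurements are scheduled at four time points in each group. The listed instruments cover several RSI domains (chronic worry and work dissatisfaction, social support, sleep, medication), so the score may be obtainable for controls. A reader might infer that controls were never screened and cannot be stratified; the article does not establish that. What stands against the objection is that the comparator is stated, without restriction, and the score that defines the subgroups is absent from the named covariates.

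The size and direction are open too. A reader might infer that the multimodal programme will look worse and the unimodal one better. That holds for follow-up level with baseline pain adjusted and a gap persisting beyond baseline pain, but not for every term a repeated-measures ANOVA can test. The unadjusted range of 0.15 to 0.40 SD should not be quoted as the expected bias, because it ignores the planned adjustment.

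Finally, this is an additional analysis. The four hypotheses under Objectives {7} concern the individualised programme as a whole. The Discussion concedes, for the comparison between subgroups, that "the power of our study is here limited, since our sample size is only intended to compare the two randomized groups". That sits awkwardly with the assurance in Trial design {8}, but it is disclosed and concerns precision. It does not address the confounding.

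**Conclusion.** The point holds as a flaw in the stated subgroup analysis and should be corrected before the data are analysed. Followed as written, the two subgroup-versus-control contrasts are not randomised comparisons, and RSI risk is confounded with treatment. Adjustment for age, sex and baseline pain would suffice only if the RSI predicted nothing beyond those covariates, which would contradict the reason for using it.

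The size cannot be computed from the article. About 0.06 to 0.17 SD is an illustration that rests on an assumed even risk split, an assumed gap of 0.3 to 0.8 SD that is the same at baseline and follow-up, and a slope of 0.57. It lies below the design effect of 0.2 but is not negligible beside it. Direction depends on the model term.

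A reader might go further and infer that the trial's main conclusion could be reversed. The document does not support that: the primary comparison is between the randomised arms and is unaffected. The statement that unimodal versus multimodal confirms the tool's discrimination is not supportable in this design, whatever the sample size.

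**What to change.** - Derive the RSI from T0 data in both arms, adding any missing RSI items to the control T0 form. Do not disclose the control scores to control patients or therapists.
- In {20b}, compare unimodal patients with low-risk controls and multimodal patients with high-risk controls. Test arm by RSI stratum in one model that includes centre, and state which model term is the estimate of interest.
- In Trial design {8}, withdraw the statement that comparing unimodal with multimodal confirms the tool's discrimination. Assess discrimination in the control arm, where care does not follow the score.

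The cost is a change of wording, scoring of control T0 answers and, where items are absent, a longer control form. Recruitment is already under way, so T0 items not collected from enrolled controls may not be recoverable; this should be checked early.

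Precision falls because each contrast uses fewer controls. With 562 evaluable intervention patients and 843 − 562 = 281 controls, an even risk split gives 281 versus about 140 instead of 281 versus 281. The standard error rises by √[(1/281 + 1/140.5) ÷ (2/281)] = √1.5 = 1.22, so intervals are about 22% wider.

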#### Control group

Patients in the control group receive the standard aftercare treatment for back pain in rehabilitation centers (“treatment as usual”). This comprises the “T-RENA,” “IRENA,” and “Reha-Sport” programs of Germany.

T-RENA is a unimodal rehabilitation aftercare program suitable for persons with impairments or functional limitations on the postural and locomotor system. It is a training supported by the use of equipment carried out in groups of up to 12 people, usually containing 26 units of 60 min each. T-RENA includes preparatory exercises for subsequent muscle building training (e.g., general endurance training, general strength training), mobility, coordination, strength, and endurance. Moreover, it aims to develop and consolidate basic motor patterns together with daily life activities, also training on compensation techniques [29].

IRENA refers to a multimodal aftercare group service for 10–12 participants. It includes up to 24 units lasting at least 90 min each. IRENA is indicated when there are persistent functional and/or cognitive limitations, the need of lifestyle stabilization, and behavioral changes, further when support on specific workplace and professional reintegration problems is required and in the transfer of skills learned at rehabilitation. Therapy is provided in at least two of the following listed services: sports and exercise therapy (endurance or muscle-building training), physiotherapy (including spinal gymnastics), motivation guidance (promotion of behavioral changes), nutrition (nutritional counseling), psychology (stress management, relaxation training, problem-oriented group work), and social work (including professional orientation). In the case of orthopedic diseases (such as chronic back pain), the services offered usually include physiotherapy, sports and exercise therapy, and group psychological work for pain management [29].

Reha-Sport consists of gymnastics, athletics, swimming, and group exercise games, which are carried out in fixed groups with a trainer. It does not include equipment training, and the duration of a unit is at least 45 min [29].

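### The subgroup analysis sets low-risk (unimodal) and high-risk (multimodal) intervention patients each against a control group not matched on risk, so prognosis can be mixed with treatment effect

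*Protocol article*

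**What the plan says.** Protocol article, Methods for additional analyses {20b}: "We also plan a subgroup analysis comparing the multimodal and the unimodal group, with the control group". Each comparison is a separate two-group repeated-measures ANOVA with "covariates such as age, sex, and baseline pain is planned for each multimodal and unimodal group".

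How the groups arise:
- Trial design {8}: patients are randomised 2:1 to intervention or control. The unimodal/multimodal split is then made by the RSI inside the intervention group only.
- Abstract, Methods: "participants in the intervention group will be screened according to their psychosocial risk profile".
- Explanation for the choice of comparators {6b}: "an initial differentiation between low-risk (unimodal) and high-risk (multimodal) groups through the RSI score".
- Control group, under {11a}: "Patients in the control group receive the standard aftercare treatment for back pain in rehabilitation centers". No division by risk is described.

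On the RSI itself, Outcomes {12} says that it "allows an estimation of the risk of low back pain chronicity (1-year prognosis) through psychosocial risk factors". Of its content it says: "It includes baseline pain, unhappiness, social support and status, distress (chronic worries), work dissatisfaction, misfortune, pain persistence, sleep problems", followed by other health care issues such as medication history and insurance status.

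The Discussion concedes limited power for comparing the two subgroups. It does not mention that the subgroups and the controls differ in risk mix.

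**The concern.** Randomisation makes the whole intervention arm comparable with the whole control arm. It does not make a risk-selected part of one arm comparable with all of the other. As the text stands, the unimodal patients are chosen for good prognosis, the multimodal patients for poor prognosis, and the controls hold both kinds.

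Adjusting for baseline pain removes only the part of this imbalance that baseline pain carries. The RSI also draws on mood, support, worries, work, sleep and pain persistence, and the listed covariates do not include the RSI.

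The analysis is not incidental. Trial design {8} justifies the 2:1 ratio partly by the wish to have enough patients in each subgroup and to confirm that the screening tool discriminates. A spurious pattern in which one modality seems to help and the other to harm would bear on that aim. Two separate tests against shared controls would also not show whether the treatment effect differs by risk class.

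**Working it through.** **The plan's own figures.** No figure is given for the subgroup analysis. From Sample size {14} I take 562 evaluable intervention patients, a total of 843, correlation 0.57 and d = 0.2. Controls: 843 − 562 = 281. The section prints 289, which does not add up to 843; the difference is immaterial here. 843/0.7 = 1204.3 agrees with the target of 1204.

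**Assumptions (not in the document).** RSI and baseline pain are standard normal with correlation 0.5. The risk split is 50:50. There is no treatment effect. The partial correlation r of the RSI with the T2 score, given baseline pain, runs from 0 to 0.3. The model is T2 adjusted for T0, a one-time-point simplification of the planned repeated-measures ANOVA.

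**Step 1: imbalance.** At a median split the low-risk half has mean RSI −0.798 and RSI variance 1 − 0.798² = 0.363. The controls have mean 0 and variance 1. Mean baseline pain in the low-risk half is 0.5 × (−0.798) = −0.399.

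**Step 2: what baseline pain removes.** Averaged over the two compared groups (281 each):
- RSI–pain covariance: (0.5 + 0.5 × 0.363)/2 = 0.341
- pain variance: [1 + (1 − 0.25 × 0.637)]/2 = 0.920
- slope of RSI on pain: 0.341/0.920 = 0.370
- RSI imbalance left after adjustment: 0.798 − 0.370 × 0.399 = 0.650

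**Step 3: bias.** The RSI effect per SD at partial correlation r is r × √(1 − 0.57²)/√(1 − 0.5²) = 0.949r. The bias is therefore 0.650 × 0.949r = 0.617r. It favours unimodal and, by symmetry, disfavours multimodal.

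**Step 4: false positives.** Without imbalance the standard error is √[(1/281 + 1/281)(1 − 0.57²)] = 0.069. The baseline imbalance raises the variance by about 4%, giving 0.071. The rejection rate is Φ(z − 1.96) + Φ(−z − 1.96), with z = bias/0.071.

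| r | bias (SD) | z | false positives |
|---|---|---|---|
| 0 | 0 | 0 | 5% |
| 0.1 | 0.06 | 0.87 | 14% |
| 0.2 | 0.12 | 1.74 | 41% |
| 0.3 | 0.185 | 2.61 | 74% |

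Simulation of the same set-up gives 0.06, 0.12 and 0.18–0.19 SD, with about 12–14%, 41–42% and 75%.

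**Step 5: like with like.** With controls restricted to the same RSI class, simulated bias is within 0.005 SD of zero and false positives are 4–6%.

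**Step 6: price of the restriction.**
- Standard error at a 50:50 split: √[(1/281 + 1/140.5)(1 − 0.57²)] = 0.085, against 0.069.
- Power for d = 0.2 without the gain from baseline adjustment: 0.2/√(1/281 + 1/140.5) = 1.94 and Φ(1.94 − 1.96) ≈ 49% per class. At a 30:70 split it is about 32% in the smaller class and 63% in the larger.
- With the adjusted standard error at 50:50: 0.2/0.085 = 2.36 and Φ(0.40) ≈ 65%.

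**The case against.** Five points can be made in the plan's defence.

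- **It is an additional analysis.** None of the four hypotheses in Objectives {7} sets unimodal or multimodal against control, and the Discussion says the sample size serves only the comparison of the randomised groups. This stands. A reader might infer that the trial's main conclusion is compromised. It is not, because the co-primary analysis in {20a} compares the arms as randomised.
- **Controls may have been scored.** The allocation flow charts are not shown, Outcomes {12} does not limit the RSI to one arm, and a separate statistical evaluation plan is mentioned under Data management {19}. So one cannot say that controls have no RSI score. That does not rescue {20b}, which names the control group without restriction.
- **The covariate list is open.** It is introduced by a phrase that allows more, so the RSI could be added. But the listed covariates leave out the variable that defines the groups.
- **Baseline pain is adjusted for and is itself part of the RSI.** If the RSI adds nothing further, the bias is zero. The RSI is described as a one-year prognosis, whereas T2 and T3 fall about 12 and 24 weeks after admission (Participant timeline {13}). A reader might infer that both results are certainly biased, by a known amount. The article supports only that bias is likely, because it gives no added prognostic value at those times.
- **Direction.** A reader might infer from unadjusted change scores that regression to the mean could reverse the bias. That reading drops the baseline-pain covariate that {20b} specifies, so it is not the planned analysis.

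**Conclusion.** The subgroup comparison is wrong as written and should be changed before analysis. It contrasts risk-selected parts of one arm with the full risk mix of the other, and no stated restriction or covariate removes the difference. Under the stated assumptions the baseline-adjusted bias runs from 0 to about 0.18 SD, and the false-positive rate from 5% to about 75%. The upper end nearly equals the effect of 0.2 SD for which the trial is sized.

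The structural fault follows from the text. The size does not: the RSI–pain correlation, the risk split and the RSI's added prognosis are all assumed. The fault is confined to the unimodal-versus-control and multimodal-versus-control results.

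**What to change.** Score the RSI at T0 in both arms with the same cut-off, and define class by that score. Replace the {20b} analysis with one model on all randomised patients containing arm, RSI class, arm × RSI class, center, age, sex and the T0 value. Report three results, all labelled exploratory:
- unimodal-assigned patients versus low-risk controls
- multimodal-assigned patients versus high-risk controls
- the interaction

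If the RSI cannot be obtained for all controls, make no unimodal-versus-control or multimodal-versus-control effect claim, or show those contrasts as non-randomised and descriptive only. Do not set only later-enrolled controls against all intervention patients, which would add a calendar-time difference.

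The cost is a change of wording and RSI scoring in controls. Whether the score can be rebuilt from the T0 questionnaires cannot be judged here, because the article names the RSI's domains but not its items, weights or cut-off. The statistical price is the larger standard error and the limited power per class shown in Step 6.
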